**Methods and analysis:**

The *Good Start in Life* study will use a quasi-experimental design (with a matched control geographical area) consisting of a combination of interventions that will build multisectoral collaboration across education, health and social services that connect and support families with children from birth to 5 years. The control area will be matched on demographic characteristics and early child development outcomes and trends over the pre-intervention period. Evaluation data will be collected at baseline, and then on an annual basis for a further three years. A mixed methods approach will be used to evaluate delivery processes: quantitative (checklists, questionnaires) and qualitative methods (observations, focus groups and key stakeholder interviews). Effectiveness of the programme will be evaluated by comparing early child development outcomes between the comparator areas from the Australian Early Development Census in 2024. The primary focus will be on reducing the number of children who are developmentally vulnerable on at least one early development index (EDI). Separate tests will be conducted for significant differences in the percentage of children at risk in each of the five individual EDI domains. These domains are physical health and wellbeing, social competence, emotional maturity, language and cognitive skills, and communication and general knowledge.

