Literature on integration between early childhood centres reports that improving collaboration between services by creating more connected and productive early childhood programmes and networks provides better opportunities for positive outcomes for children and families [14]. Further studies have shown that the creation of a “virtual” network in which services do not need to relocate to a singular location produces the same benefits as co-located services [15].

As the nature of service integration prohibits a singular definition, a fit-for-purpose, context-and cultural- specific definition needs to be developed. In this project, the development of a definition will be considered as an outcome as this is an iterative process and will be refined throughout the project to represent the context, nature, and function of the integrated network most accurately. Broadly, this project views service integration as the creation of or strengthening of agency between early childhood services and programs across sectors within the local area. Such integration should provide a more comprehensive connection for families and greater numbers and quality of developmental opportunities for children, leading to better outcomes.

This project aims to evaluate an intervention designed to integrate child and family services within the district and embed allied health programs into early childhood education and care services and playgroups and to evaluate the outcomes and processes of the intervention. The Project Management Team (PMT) collaborate with local services to form a network of related services for children aged between birth and 5 years across the health, education, and social services sectors, allowing families to more easily access and navigate through different services.

The two main aims for this project are:

To create an integrated network of services for young children and families in target suburbs in the Belconnen district in the ACT.To reduce the proportion of developmentally vulnerable children in the target suburbs of the Belconnen district in the ACT.

The following questions will be addressed:

Does a multi-sector, multi-component approach reduce the proportion of children who are considered developmentally at risk in the intervention community compared to the control community?What is the reach, participation, intervention quality and dose of the interventions delivered and what were the barriers to, and facilitators of, implementation?

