## Methods and analysis

### Design and intervention

This study will use a quasi-experimental design to determine the effectiveness of creating an integrated service network on reducing developmental vulnerability in young children. The formative components of the project commenced in November 2020 and the project will conclude in March 2024. The intervention will take place in the Belconnen district, chiefly within services located in the nine identified target intervention suburbs, while the Tuggeranong district will serve as the ‘control’ site. These two districts are well-matched on socio-demographic characteristics and on early child development outcomes from the most recent three censuses. Data will be collected from the AEDC for comparison, but no intervention will occur within this district other than those that are to be expected in a large urban area. The intervention will be conducted using a ‘staggered’ approach, starting with four suburbs (in two clusters) in the first year and ending with all nine suburbs (four clusters) receiving the intervention by the fourth year. An integrated multi-sector programme will be delivered to children and families in multiple settings in the intervention suburbs through a wide range of programmes and services that focus on the 5 AEDC domains of childhood development: physical health and wellbeing, social competence, emotional maturity, language and cognitive skills, and communication and general knowledge. The list of programs to be implemented are presented in Appendix 1 in S1 File. To help achieve key aims of this project, a family liaison coordinator will be employed. The role of this coordinator will be to work within the community to connect families to services and to facilitate the creation of referrals for children with additional needs. In addition, the family liaison coordinator will work with services to better connect them to other related services and to the wider community.

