#### Quantitative analysis

Testing for statistically significant differences in children’s early development indices will be based on the critical difference approach developed for the AEDC by Gregory and Brinkman [17]. The Gregory and Brinkman report provides the technical details to determine “how big” a difference (%) needs to be in the EDI results between two different time points or two different areas to be considered statistically significant [11, Tables 14 –primary outcome and 13 –the five secondary outcomes, respectively]. The method allows for the expected sample to sample variation and typical measurement error associated with the sort of data collected in the AEDC. Current versions of the methodology allow us to compare two point-estimates, either across time or between neighbourhoods, of the selected index. Table 1 shows the critical differences that will be needed to establish a significant change for each of the six EDI indices,—the primary outcome and five secondary outcomes—to be considered in this study. The population of children in the intervention and control areas is expected to be in the range 200–299 at the 2024 census. Time-point comparisons will be made between 2021 and 2024 AEDC indices for both intervention and comparator areas. Across-area comparisons will be made between intervention and comparator areas for the 2024 census indices. The following hypotheses will be tested for each of the six indices to be used in this study:

Each EDI for the intervention suburbs (within the Belconnen district) for the 2024 census will be significantly lower, i.e. show a significant reduction in the proportion of children who are developmentally vulnerable or at risk, compared to that in the control suburbs (within the Tuggeranong district)Each EDI for the intervention suburbs (within the Belconnen district) for the 2024 census will be significantly lower, i.e. show a significant reduction in the proportion of children who are developmentally vulnerable or at risk, compared to the corresponding value in the 2021 census

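### No planned test contrasts the intervention area's change with the control area's change, so the 2024 comparison answers the effectiveness question only if the two sets of suburbs started level

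*Protocol article*

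**What the plan says.** The Introduction's first research question is whether the programme will "reduce the proportion of children who are considered developmentally at risk in the intervention community compared to the control community". The abstract describes a "quasi-experimental design (with a matched control geographical area" and says: "Effectiveness of the programme will be evaluated by comparing early child development outcomes between the comparator areas", using the 2024 census.

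The Quantitative analysis section then fixes two kinds of test. One is between areas: "Across-area comparisons will be made between intervention and comparator areas for the 2024 census indices". The other is within area, 2021 against 2024, for intervention and comparator separately. The two listed hypotheses are that each index in the intervention suburbs in 2024 will be lower than in the control suburbs in 2024, and lower than its own 2021 value. The section describes the test method in these terms: "Current versions of the methodology allow us to compare two point-estimates, either across time or between neighbourhoods, of the selected index". The sample size paragraph repeats the same comparisons.

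On comparability, the abstract states: "The control area will be matched on demographic characteristics and early child development outcomes and trends over the pre-intervention period". Design and intervention adds: "These two districts are well-matched on socio-demographic characteristics and on early child development outcomes from the most recent three censuses". Participants explains that suburbs were considered for the intervention if vulnerability had worsened over the 2012, 2015 and 2018 censuses.

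**The concern.** A reduction relative to a control is a contrast of two changes and needs four estimates: each area before and after. The plan tests pairs. The between-area hypothesis has no baseline term, so any gap that existed beforehand is read as programme effect or hides it. The before-after hypothesis has no control term, so any shift common to the territory is read as programme effect. The control area's change is to be examined but enters no hypothesis, and no estimate, threshold or test of the difference in change is stated.

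This is not detail left to an analysis plan. The article positively states the comparisons, the hypotheses and a method limited to two estimates. At stake is the study's main conclusion on effectiveness.

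**Working it through.** **Inputs.** Critical difference for the primary outcome, 4.7 percentage points for 200–299 children (Table 1). Expected 200–299 children in the intervention and control areas (Quantitative analysis). Rate 26.4% for Belconnen in 2018 (Introduction); about 40% in the sample size text. The article states no alpha.

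**Can 4.7 be reproduced?** Not from the article, because the error model lies in the cited technical report. A two-sample 95% binomial margin, 1.96 × √(2p(1−p)/n), gives 7.1 to 8.6 points at p = 0.264 and 7.9 to 9.6 at p = 0.40 (n = 299 to 200). The structural point does not depend on this. The illustrations below take 4.7 at face value as a two-sided 5% threshold, so SE = 4.7/1.96 = 2.40 points.

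**Before-after hypothesis, no programme effect.** If both areas fall by s points for outside reasons, the probability of meeting the hypothesis is Φ((s − 4.7)/2.40):
- s = 0: 2.5%
- s = 2: 13%
- s = 4.7: 50% (by construction, since the shift equals the threshold)

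**2024 between-area hypothesis, no programme effect.** If the intervention suburbs already stood g points lower, the probability is Φ((g − 4.7)/2.40):
- g = 0: 2.5%
- g = 2: 13%
- g = 3: 24%

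**Gap in the other direction.** For a true 6.6-point effect with the intervention suburbs starting g points higher, power is Φ((6.6 − g − 4.7)/2.40):
- g = 0: 79%
- g = 2: 48%
- g = 3: 32%

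**What the missing contrast needs.** A difference in change combines four independent estimates instead of two, so its SE is √2 times as large:
- Threshold scaled from Table 1: 4.7 × √2 = 6.6 points (equal, independent errors).
- Binomial SE, 250 children per cell, p = 0.264: √(4 × 0.264 × 0.736/250) = 5.6 points.
- Three pre-waves pooled: √(2 × 0.264 × 0.736 × (1/250 + 1/750)) = 4.6 points (4.55).
- Binomial 95% threshold for n = 299 to 200: 10.0 to 12.2 points at 26.4%, and 11.1 to 13.6 at 40%.
- Power for a 4.7-point effect at two-sided 5%: about 13% with SE 5.58 and about 18% with SE 4.55, before any allowance for suburb clustering.

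**The case against.** The strongest reply is that baseline is handled by design. The control is matched on earlier outcomes and trends. If levels really were equal, the 2024 comparison estimates the effect, and more precisely: at 250 per cell its binomial SE is 5.58/√2 = 3.9 points against 5.6 for the difference in change. That stands as a conditional argument, but the article does not establish the condition. Matching is described for Belconnen and Tuggeranong as districts, the test concerns suburbs within them, the intervention suburbs were selected on worsening, and no control baseline figure is reported.

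A reader might infer that the study cannot answer its first research question at all. The documents do not support that, because the 2024 test answers it if starting levels were equal. A reader might also infer that success will be declared when the intervention's change is significant and the control's is not. No such rule appears; neither hypothesis compares verdicts. Nor is the article silent on which comparison carries the conclusion: the abstract points to the 2024 between-area comparison, although the Developmental vulnerability section describes a two-timepoint test for the same outcome, so the two need reconciling.

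The Discussion is also cautious about attribution and acknowledges concurrent programmes. That tempers interpretation but does not change the tests.

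**Conclusion.** The point holds in this form: the stated analysis never contrasts the two areas' changes, and each planned test rests on a condition that the article does not secure. For the 2024 test the condition is equal prior levels in the suburbs compared; for the before-after test it is no common change between censuses.

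Shifts or gaps well below the study's own 4.7-point threshold matter. A shift or gap of 2 points raises the chance of a false positive conclusion from 2.5% to 13%. These figures assume SE = 4.7/1.96 and hypothetical gaps and shifts; the article gives neither the control's baseline nor any expected secular change, so the actual bias and its direction are unknown. Since the suburbs were picked for worsening, a gap that masks benefit is as much a possibility as one that mimics it.

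**What to change.** 1. Reconcile the baseline census. Developmental vulnerability sets 2018 as baseline and excludes 2021; the sample size text and Quantitative analysis test 2021 against 2024. No change can be defined until this is settled.
2. Make the primary effectiveness analysis the between-area difference in the change, from that baseline to 2024, in the proportion vulnerable on at least one domain. Report the estimate with a 95% CI from suburb-level census data, allowing for suburb-level variation. Keep the two pairwise comparisons as supporting results.
3. Do not apply the 4.7-point threshold to this contrast.
4. Show 2012–2018 trends in both areas as a sensitivity check, and say plainly that choosing suburbs on those same trends leaves regression to the mean that a difference-in-differences does not remove. Nor does it remove the effect of the other project running in Belconnen.

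**Cost.** No new collection appears necessary: 2012–2018 suburb data were used for selection, and the Discussion says suburb-level data are released. But this is more than a wording change. The two-estimate method, the Table 1 threshold and the sample-size basis need replacing for this contrast. The interval will be wider and power for a 4.7-point effect low. Nine suburbs sharing 200–299 children give about 22 to 33 each (200/9 to 299/9), so suburb-level inference will be limited.

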## Discussion

In this paper, we present the design of a quasi-experimental study in which we conduct a process and outcomes evaluation of a multi-sector, multi-component programme of interventions for improving the physical and mental health of children who are at the highest risk of developmental vulnerability and disadvantage in the ACT. The focus of providing a family liaison coordinator in important behaviour settings within the child’s environment, i.e., early childhood education, playgroups and community settings, is considered a strength of this intervention.

The interventions will be implemented in collaboration with local professionals and community members. Community co-design during conceptualisation, development and planned implementation is central to this study. Participatory approaches ensure end-users and service provider voices are heard and provide an understanding of local practice and context to ensure more authentic engagement with community members in the target areas.

In addition to the outcome evaluation, a process evaluation will be conducted to provide insights into the implementation of the interventions and the role of the local context. The link between effectiveness and implementation are important for developing and scaling future health promotion interventions.

To monitor intervention effectiveness multiple data collection tools are used to measure the different outcomes. Firstly, fidelity measures are collected to ensure the programs and interventions are implemented as intended. Incorrectly or incompletely implemented programs may result in the intervention having no effect on educator professional knowledge and practice, and therefore these measures must be collected to account for any lack of significant differences in the primary outcome measure. These outcomes will be detailed in the process evaluation. Other data collected, including the AEDC results, service integration survey scores, and data from the speech pathology and occupational therapy programs, will be used to form the outcome evaluation. This evaluation is used to assess the extent to which the project delivered the outcomes outlined in the planning program logic and if there were any significant improvements in developmental vulnerability in children in the Belconnen district that may have been influenced by this project.

This study has several limitations. The primary limitation arises from the use of the AEDC data. For confidentiality and privacy, the AEDC only releases suburb level data. However, it is widely understood that children do not always attend ECECs and services within the suburb in which they live. As a result, providing place-based interventions within intervention suburbs may not reach as many children from that suburb as intended. The study will collect data on which suburb each child attending a program or service lives in, but purposely excluding children from other suburbs is not possible as it is unethical and defies the universal nature of the programs and services provided.

It is known to the PMT that another similar project is operating in the Belconnen District at the same time as the Good Start in Life project. Whilst efforts have been made to regularly communicate and collaborate with the other project, there is the chance that their work may interfere with the two primary outcome measures of this project. Additionally, early childhood education centres, services and programs may elect not to engage with the study and to conduct their own professional development practices or engage with other services on their own. This may also influence the data this project is collecting on child development outcomes and service integration.

Finally, there is the chance that similar projects and interventions may operate within the control site, the Tuggeranong District. Once again, it is unethical and unfeasible to prevent other research teams or organisations from implementing similar programs in that area. However, throughout the study we will record any new programmes/services that are delivered in this control area.

### Patient and public involvement statement

Extensive consultation with key services and local stakeholder organisations/groups have been undertaken to inform study design and programme implementation. An advisory board has been established with representation from key partners (and from health, social care and education sectors) which meets every three months.
